## Abstract

**Background:**

Chronic subdural hematoma (cSDH) is the most common complication of mild traumatic brain injury demanding neurosurgery in high-income countries. If undetected and untreated, cSDH may increase intracranial pressure and cause neurological deficiencies. The first-line intervention of choice is burr hole trepanation and hematoma evacuation. However, any third patient may experience rebleeding, demanding craniotomy with excess morbidity. Adjunct endovascular embolization of the frontal and parietal branches of the middle meningeal artery (MMA) is a promising approach to avoid relapse and revision but was hitherto not studied in a randomized trial.

**Methods:**

MEMBRANE is an investigator-initiated, single-center, randomized controlled trial. Male, female, and diverse patients older than 18 years scheduled for surgical evacuation of a first cSDH will be assigned in a 1:1 fashion by block randomization to the intervention (surgery plus endovascular MMA embolization) or the control group (surgery alone). The primary trial endpoint is cSDH recurrence within 3 months of follow-up after surgery. Secondary endpoints comprise neurological deficits assessed by the modified Rankin Scale (mRS) and recurrence- or intervention-associated complications during 3 months of follow-up. Assuming a risk difference of 20% of rebleeding and surgical revision, a power of 80%, and a drop-out rate of 10%, 154 patients will be enrolled onto this trial, employing an adaptive O’Brien-Fleming approach with a planned interim analysis halfway.

**Discussion:**

The MEMBRANE trial will provide first clinical experimental evidence on the effectiveness of endovascular embolization of the MMA as an adjunct to surgery to reduce the risk of recurrence after the evacuation of cSDH.

**Trial registration:**

German Clinical Trials Registry (Deutsches Register Klinischer Studien [DRKS]) DRKS00020465. Registered on 18 Nov 2021. ClinicalTrials.gov NCT05327933. Registered on 13 Apr 2022.

## Administrative information

Note: the numbers in curly brackets in this protocol refer to SPIRIT checklist item numbers. The order of the items has been modified to group similar items (see http://www.equator-network.org/reporting-guidelines/spirit-2013-statement-defining-standard-protocol-items-for-clinical-trials/).

## Introduction

### Background and rationale {6a}

Chronic subdural hematoma (cSDH) is the most frequent complication of mild traumatic brain injury requiring neurosurgical care, and the most common type of traumatic intracranial hemorrhage in high-income countries alike [1]. The reported annual incidence of cSDH ranges from 1.7 to 20.6 per 100,000 [2], with a significant increase noted during the past years. The latter is attributed to a more liberal use of computed tomography (CT) and magnetic resonance imaging (MRI), as well as to demographic changes [3].

Pathogenesis of cSDH comprises fibrinolysis and liquefication of the initial blood clot, secondary local inflammatory response, and subsequent formation of space-occupying subdural neo-membranes up to ten days after injury [4, 5]. Apart from older age, known risk factors of cSDH are male gender, therapeutic anticoagulation and bleeding disorders, alcohol abuse, diabetes mellitus, and arterial hypertension [6–8]. Specifically, subnormal factor XIII activity due to polymorphism in coding genes F13A1 rs2815822 [9] and F13B rs12134960 [10] is associated with an enhanced risk of postoperative intracranial bleeding [11].

Non-operative management with serial cranial CT monitoring may be suitable for small, asymptomatic hematomas, while symptomatic cSDH almost always needs neurosurgical intervention [12]. Burr hole trepanation is regarded as the current standard of care, with acceptable morbidity and mortality [13–16]. Still, recurrent cSDH occurs in up to one-third of cases after surgery [17, 18].

A meta-analysis of 250 studies enrolling 34829 patients showed substantial heterogeneity due to varying definitions of recurrence [13]. In a retrospective analysis of patients younger than 45 years with cSDH, the incidence of recurrent bleeding was estimated at 7/29 (24%) [19].

Several options were proposed to lower the risk of recurrence and reoperation (i.e., Ommaya reservoirs placed in the subdural space, endoscopically-assisted surgery, systemic carbazochrome, or glucocorticoids), none of which turned out to be markedly effective.

Embolization of the middle meningeal artery (MMA) by polyvinyl alcohol (PVA) particles, liquid embolic agents such as Onyx® (Medtronic, Dublin, Ireland), and/or coiling is a promising interventional adjunct to surgery for cSDH [17, 20, 21], which may also prevent micro-bleeding from cSDH membranes [17]. It has been established as a safe procedure [16, 17, 20, 22–27] in clinical practice for various other indications (e.g., dural arteriovenous fistulas, meningiomas) [28, 29]. Although single cases of cranial nerve palsy and blindness were reported [30, 31], the risk of adverse events may be minimized by excluding anastomoses between intra- and extracranial vessels [32].

Ban et al. conducted an observational study of primary endovascular management of patients with cSDH compared to a historical cohort undergoing the standard of care [20]. Recurrence risks were 1/72 (1.4%) and 129/469 (27.5%), respectively, for an adjusted odds ratio [OR] of 0.056 (95% CI 0.011 to 0.286). Patient selection was conditional on space-occupation by cSDH, with a higher likelihood of surgery with larger blood collections.

The Middle Meningeal Artery Embolization Minimizes Burdensome Recurrence Rates After Newly Diagnosed Chronic Subdural Hematoma Evacuation (MEMBRANE) trial aims at investigating the effectiveness and safety of supportive MMA embolization after surgical evacuation of cSDH.

### Objectives {7}

#### Primary objective

The primary objective of this study is to investigate whether surgical hematoma evacuation plus endovascular embolization of the MMA lowers the risk of cSDH recurrence compared to surgery alone.

#### Secondary objectives

Secondary objectives of this study include the assessment ofNeurological deficits,Recurrence-associated complications, andComplications associated with endovascular embolization.

#### Tertiary objectives

Tertiary objectives of the study are to investigateThe relationship between factor XIII deficiency and risk of recurrence andThe association between the genetic variants F13A1 rs2815822 and F13B rs12134960 with factor XIII activity.

### Trial design {8}

MEMBRANE is an investigator-initiated, single-center, randomized controlled trial testing whether neurosurgical hematoma evacuation plus endovascular embolization of the MMA (intervention group) is superior to surgery alone (control group) in reducing the recurrence rate of cSDH within a follow-up period of 3 months. Eligible patients will be allocated in a 1:1 ratio to either the intervention or control group (see study flowchart in Fig. 1).

**Fig. 1 Fig1:**
[figure not shown]
Study flowchart

## Methods: participants, interventions, and outcomes

### Study setting {9}

The MEMBRANE trial will be conducted at the BG Klinikum Unfallkrankenhaus Berlin (ukb) in Berlin, Germany. The ukb is a tertiary care, academic teaching hospital, and certified supra-regional trauma center with more than 730 beds, 17 operating theatres, a dual-use helicopter, and one of the busiest interdisciplinary stroke units in the capital of Germany. Given its mobile stroke unit and wide-ranging tele-neurology service, the ukb emerged as a premier national referral institution for acute neurological and neurosurgical cases [33, 34].

All clinical investigators are board-certified and have renowned expertise in neurosurgery, neuroradiology, and endovascular interventions. Structural and process quality in terms of state-of-the-art radiological imaging, surgery, critical care, and management of complications are provided, subject to federal quality assurance and maintenance measures. Research is facilitated by a distinct methodological center, guaranteeing compliance with and adherence to ICH-GCP, data safety measures (i.e., EU-GDPR), and all relevant ethical and reporting standards.

### Eligibility criteria {10}

#### Inclusion criteria

Patients scheduled for surgery by means of one or more burr hole trepanations during the first manifestation of a cSDH (unihemispherical or bihemispherical), as detected by CT or MRIAge ≥18 yearsWritten informed consent of the patient to participate in the trialLikely compliance of the participant in attending follow-up examination

#### Exclusion criteria

Conservatively treated cSDHAge <18 yearsRadiological evidence of an acute or subacute subdural hematoma, subarachnoid hemorrhage, intracerebral hematoma, or epidural hematomaPrimary craniotomy, craniectomy, or bilateral burr hole trepanationAngiography cannot be performed within 72 h after surgerySupervisory relationshipPregnancyLack of informed consentLikely lack of complianceHomozygous factor XIII activity <10%

### Who will take informed consent? {26a}

The investigator or her/his representative (at least a board-certified physician) of the Department of Neurosurgery or Department of Radiology and Neuroradiology at the ukb will approach eligible patients, hand out an informed consent form, and explain (in plain language) the rationale, design, risks, and potential benefits of the study. Patients will be given ample of time to ask questions, and are requested to provide written informed consent within 24 h.

### Additional consent provisions for collection and use of participant data and biological specimens {26b}

Patients willing to participate in the sub-study on factor XIII activity of this trial must provide extra consent for genetic analyses in accordance with the German Act of Genome Diagnostics (“Gendiagnostikgesetz”, https://www.bundesgesundheitsministerium.de/service/begriffe-von-a-z/g/gendiagnostikgesetz.html).

Relevant patient information and consent forms were approved by the IRB (Charité University Medicine Berlin, Germany, EA1/119/19) in October 2019.

## Interventions

### Explanation for the choice of comparators {6b}

Patients assigned to the control group will be managed according to the current standard of care, i.e., neurosurgical evacuation of cSDH by burr hole trepanation and/or any surgical technique without specific added treatment.

### Intervention description {11a}

Patients assigned to the experimental arm will undergo neurosurgical evacuation of cSDH by burr hole trepanation and/or any surgical technique plus endovascular embolization of the MMA (see Fig. 2).

**Fig. 2 Fig2:**
[figure not shown]
Lateral angiograms of the MMA before embolization (**A**) and after injection of 0.5 ml PVA particles (100–300μm) obstructing the peripheral branches of the MMA (**B**)

The embolization procedure can briefly be described as follows: A micro-catheter is inserted via a transfemoral approach into the branches of the MMA in a minimally invasive manner, and the periphery is occluded using PVA particles to prevent future bleeding. For this purpose, the micro-catheter is positioned as distally as possible, which prevents dislocation of particles into nutritive branches [29, 35]. If the desired catheter position cannot be achieved due to anatomical conditions, the MMA can optionally be closed more proximally using Onyx® or micro-electric coils. Embolization of the MMA by PVA particles with sizes between 40 and 300 μm is preferred over embolization by coils and Onyx®, since the capillary network of the dura is entirely blocked when using particles [35]. After using coils, a faster reperfusion via collaterals might be possible.

Target vessels are identified by digital subtraction angiography (DSA) in patients assigned to the intervention group, meaning increased exposure to radiation. Based on embolization of MMA branches in meningioma patients, a dose area product (DAP) of about 6000 to 16,000 centi-gray centimeter squared (cGy per cm^2^) is expected depending on the extent of embolization and individual anatomy. Thus, it is very much unlikely the DAP associated with the experimental adjunct exceeds the reference value for neuroradiological interventions of 20,000 to 30,000 cGy per cm^2^ as defined by the Federal Office for Radiation Protection of Germany (“Bundesamt für Strahlenschutz”, BfS). The trial and imaging protocol was approved by the BfS on March 25, 2022, under notification reference ZD 3-22464/2022-015-A.

### Criteria for discontinuing or modifying allocated interventions {11b}

Patients may withdraw their consent at any time without providing a reason and thus terminate their participation in the study prematurely. Withdrawal from the study and reasons, if known, will be documented. Criteria for premature drop-out include:Subsequent occurrence of an exclusion criterionLoss of contactDeathDeclaration of withdrawn consent

Moreover, the principal investigator is entitled to terminate the study prematurely if:Patient recruitment remains inadequate despite multiple measures to improve enrolmentSerious problems with the quality of collected data cannot be resolvedUnforeseeable circumstances at the trial center prevent trial continuationUnacceptable risks arise (after a risk-benefit assessment by the Data Safety Monitoring Board)New scientific findings in favor of one or the treatment violate the equipoise principle

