### Participant timeline {13}

Participants in the intervention and control groups will undergo five and four scheduled follow-up visits, respectively (Table 1):*−t*_1_ Screening and informed consent*t*_0_ Randomization*t*_1_ Baseline*t*_2_ Embolization (intervention group only, within 72 h after surgery)*t*_3_ Follow-up 1 month after baseline (± 1 week)*t*_4_ Follow-up 3 months after baseline (± 1 week)

**Table 1 Tab1:** Schedule of enrollment, interventions, and assessments

	Study period					
	Enrollment	Allocation	Post-Allocation			Close-Out
Time point	*−t*_*1*_	*t*_*0*_	*t*_*1*_	*t*_*2*_	*t*_*3*_	*t*_*4*_

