## Assignment of interventions: blinding

### Who will be blinded {17a}

Due to the surgical and interventional nature of trial modalities, blinding of both the immediately performing clinical investigators (i.e., neurosurgeons and interventional radiologists) and patients is almost impossible. While a sham procedure (i.e., placement of a transfemoral catheter and even infusion of a saline placebo) in the control group may be implemented, this is considered unethical as it exposes patients to additional harm without any possible benefit, given the primary endpoint.

Radiological experts evaluating baseline and follow-up CT scans after 1 and 3 months will be blinded to the randomly assigned treatment, assuring this is an observer-blinded trial.

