### Plans for collection, laboratory evaluation, and storage of biological specimens for genetic or molecular analysis in this trial/future use {33}

Blood drawn from patients at baseline will routinely be analyzed for platelet count, activated partial thromboplastin time (aPTT), and fibrinogen concentration. For study purposes, we will analyze factor XIII concentration by means of STA-R (Stago, Düsseldorf, Germany) with HEXAMATE Factor XIII (Roche Diagnostics, Basel, Switzerland), and the presence of genetic variants F13A1 rs2815822, F13B rs12134960, F13A1 rs2815822 (C > A) and F13B rs12134960 (C > G). To determine factor XIII activity, blood samples will be cryopreserved for later analysis.

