### Methods in analysis to handle protocol non-adherence and any statistical methods to handle missing data {20c}

The primary analysis will be performed on the modified intent-to-treat (mITT) set including all randomized patients and based on the treatment arm they were randomized to, regardless of the therapy they actually received. The modification of the ITT set implies that study outcomes must be fully documented at the follow-up visit at 3 months. The per-protocol (PP) set is used for sensitivity analyses, including participants who were treated in full accordance with the study protocol and actually received the randomly assigned treatment.

A missing data analysis will be conducted investigating the extent and type of missing values in trial endpoint variables. In case of a suspected non-random missing data mechanism (e.g., Missing At Random [MAR], Missing Not At Random [MNAR]), corresponding sensitivity analyses will be carried out along with a discussion of the results. If suitable, we will consider multiple imputation (MI) to fill empty cells in the dataset.

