### Adverse event reporting and harms {22}

All SAEs reported by study participants or observed by an investigator within the study period must be documented in the eCRF. SAEs are any undesirable sign, symptom, or medical condition whichIs fatalIs acutely life-threateningRequires or prolongs inpatient hospitalizationResults in persistent or significant disability/incapacityConstitutes a congenital anomaly or birth defect (not applicable, pregnancy excludes from study participation)

The principal investigator will be informed immediately about the onset of a SAE and must decide whether the participant shall be excluded from or remain in the study. The likelihood of a causal relationship between the individual trial intervention and SAE will be investigated further, and patients will be observed until the SAE resolves or a stable condition is reached.

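### Later exclusion criteria, death and post-SAE exclusion can take randomised patients out of the primary analysis, contrary to its stated intention-to-treat basis

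*Protocol article*

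**What the plan says.** All references are to the protocol article.

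- **Drop-out.** Section {11b}: "Criteria for premature drop-out include:Subsequent occurrence of an exclusion criterionLoss of contactDeathDeclaration of withdrawn consent".
- **After an SAE.** Section {22} says that the principal investigator "must decide whether the participant shall be excluded from or remain in the study". The wording concerns the study, not the study treatment, and no criteria are given.
- **Exclusion criteria.** The list in {10} includes angiography that cannot be done within 72 h of surgery, and radiological evidence of acute or subacute subdural, subarachnoid, intracerebral or epidural bleeding.
- **Timeline.** Section {13} puts randomisation at t0, baseline at t1 and, at t2, "Embolization (intervention group only, within 72 h after surgery".
- **Complications.** Section {18a} lists epidural haematoma after perforation of the artery as a complication of embolisation.
- **Primary analysis set.** Section {20c} describes it as "including all randomized patients and based on the treatment arm they were randomized to, regardless of the therapy they actually received". The next sentence restricts it: "The modification of the ITT set implies that study outcomes must be fully documented at the follow-up visit at 3 months".
- **Retention.** Section {18b} keeps data for the final analysis, unless deletion is demanded, from patients who choose to stop, do not respond or cannot be reached.

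**The concern.** An exclusion criterion is meant to act before allocation. Section {11b} lets it act afterwards, and two of the criteria in {10} can arise then.

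The 72-h angiography criterion has practical meaning only where an angiogram is due, which is the embolisation arm. A control patient has no procedure that could fail to take place. Removal on this ground therefore follows the assigned arm.

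New acute, subacute or epidural bleeding is close to the primary outcome. Epidural haematoma is also a safety outcome of embolisation, so the same event can be counted as a harm and be a reason to leave the trial.

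The SAE route adds to this. A recurrence that needs surgery will usually require or prolong a hospital stay, which is one of the SAE criteria in {22}. The primary event itself can thus open an exclusion decision that has no stated rules.

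Death is on the drop-out list too, although it is a level (6) of the modified Rankin scale, a secondary outcome.

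If such patients have no 3-month visit, they fail the documentation condition in {20c}. The arms then compared are no longer the arms that were randomised.

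**Working it through.** **1. The text side by side.**

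| Section | What it does to a patient removed on day 3 |
|---|---|
| {11b}, {22} | Permits the removal |
| {20c}, first statement | Keeps the patient, by assigned arm |
| {20c}, second statement | Drops the patient unless 3-month outcomes are complete |
| {18b} | Does not mention patients whom the investigator excludes |

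These statements cannot all be followed. Section {18b} also conflicts with the 3-month condition for the patients it does cover: their data are to be used, yet they lack the visit.

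**2. The plan's own numbers.** Section {14} assumes 30% against 10%, power 80% and alpha 5%, with 69 evaluable per arm. The unpooled formula (1.96 + 0.8416)² × (0.30 × 0.70 + 0.10 × 0.90) / 0.20² gives 58.9 per arm. With the continuity correction it is 68.5, so 69. Then 69 / 0.9 = 76.7, so 77 per arm and 154 in all. The sample size reproduces. It allows 77 − 69 = 8 losses per arm.

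**3. Worst case under no true effect.** Assumptions, none of them from the documents: recurrence p = 25% in both arms, 69 per arm before removal, and a fraction q of embolisation-arm patients removed, all of whom had a recurrence. The apparent rate in that arm is (p − q) / (1 − q), on about 69 × (1 − q) patients. The last two columns give the probability that the chi-square test is significant in favour of embolisation at the final level of 0.0469 in {20a}, by exact enumeration.

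| q | Left in embolisation arm | Apparent rate | Removal in that arm only | Same removal in both arms |
|---|---|---|---|---|
| 0 | 69 | 25.0% | 2.3% | 2.3% |
| 2% | 68 | 0.23/0.98 = 23.5% | 3.8% | about 2.3–2.5% |
| 5% | 66 | 0.20/0.95 = 21.1% | 7.6% | about 2.3–2.5% |
| 8% | 63 | 0.17/0.92 = 18.5% | 13.7% | about 2.3–2.5% |

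These rates are one-sided, while the plan's test is two-sided. On a two-sided scale, with 30% in both arms and 10%, 20% or 30% of the embolisation arm's recurrences removed (about 2, 4 or 6 patients), the rejection rate is about 5.5%, 8.4% or 13.8%.

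**4. Fragility of the planned result.** The planned rates correspond to about 21/69 against 7/69, p = 0.003. Put back k removed embolisation patients, all with recurrence:

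- k = 5: 12/74, p = 0.044
- k = 6: 13/75, p = 0.064, no longer below 0.0469
- k = 8, the full allowance for one arm: 15/77, p = 0.125

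**The case against.** The best defence is that {20c} states an intention-to-treat principle, and also foresees a missing-data analysis, sensitivity analyses and possibly multiple imputation. This shows the intent and softens the problem. It does not remove it, because the primary set stays restricted and imputation is only to be considered if suitable. Nor does the article say outright that an excluded patient has no 3-month visit; the point is that its wording allows this.

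A reader might infer more than the text supports:

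- **Rebleeds vanish from the embolisation arm and stay in the control arm.** The bleeding criterion in {10} is written for both arms, and both have CT at 1 and 3 months. Removal in one arm only is a worst case, and a bias in favour of embolisation is not established. An acute bleed is also not automatically the recurrent chronic haematoma that defines the outcome.
- **An unblinded principal investigator decides.** Section {17a} says "blinding of both the immediately performing clinical investigators (i.e., neurosurgeons and interventional radiologists) and patients is almost impossible". It does not say whether the principal investigator is among them.
- **Conversion to craniotomy is an exclusion.** Section {10} excludes primary craniotomy; a conversion during surgery is not plainly that.
- **The factor XIII criterion biases the comparison.** Section {33} says "To determine factor XIII activity, blood samples will be cryopreserved for later analysis", so a value may come late. It is nevertheless a baseline property that applies to both arms and is unrelated to assignment.
- **Allocation always precedes surgery.** The abstract describes patients "scheduled for surgical evacuation of a first cSDH will be assigned in a 1:1 fashion by block randomization", but the timeline does not place surgery relative to randomisation. The point does not need this, since t0 precedes t2 in any case.

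**Conclusion.** The point holds as a contradiction in the plan with a possible bias in the primary comparison. Sections {11b} and {22} permit removal after randomisation on grounds tied to the embolisation step or to bleeding. The 3-month condition in {20c} can then take those patients out of the primary analysis, and {18b} does not cover them.

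The documents give no removal rate, so neither the size nor the direction of bias can be stated. Under the assumed one-arm removal the one-sided error lies between 3.8% and 13.7%, against 2.3% without removal. With equal removal it hardly moves. What matters is that a handful of patients, fewer than the eight losses per arm that the plan allows for, could decide the result. This should be fixed, ideally before the interim analysis.

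**What to change.** Reconcile {11b}, {18b}, {20c} and {22}:

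1. In {11b}, delete the later occurrence of an exclusion criterion as a reason to leave the study.
2. In {22}, limit the principal investigator's decision to study treatment.
3. Follow every randomised patient to 3 months unless consent is withdrawn.
4. In {20c}, include all randomised patients by assigned arm in the primary analysis. Count a recurrence observed before death or discontinuation as an event, and use the missing-data methods already foreseen for outcomes that are truly unknown.
5. Align {18b}, so that it also covers patients whom an investigator takes off study treatment.

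Moving randomisation to after surgery, or rewriting the factor XIII exclusion, is not needed for this.

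The cost is a short amendment, some extra follow-up and missing-data work, and a slightly diluted effect from patients who do not receive embolisation. For illustration, if 5% of that arm were not embolised and carried the control risk, the expected rate would be 0.95 × 10% + 0.05 × 30% = 11%, and the risk difference 19% instead of 20%. Clinical management is untouched.
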